### Using theory to design an enhanced feedback intervention

Briefly, performance feedback may be understood to work by directing attention toward a discrepancy between an expected or desired state and reality [12]. When present, this discrepancy may encourage the recipient to generate increased effort toward the goal, especially if the next steps or sub-goals are clear. Alternatively, the feedback may be perceived as inaccurate and disregarded, or the feedback may result in the recipient lowering their goal to make it more achievable [13]. To be effective, the ideally designed feedback would consistently lead to changes in behaviour by the recipient through increased efforts to reach appropriate goals.

There are both theoretical and empirical reasons to believe that feedback will be more effective if the recipients set goals [14] and develop action plans [15]. According to Goal-Setting Theory [16], those who are dissatisfied with their performance will develop a change in behaviour if they are committed to the goal and if they meet a threshold level of self-efficacy for that task. Bandura explains that people are more likely to try to accomplish a goal if they believe their efforts will be successful [17].

Psychologists have repeatedly shown that detailed plans regarding where/when/how behaviours will be enacted increases the likelihood of task accomplishment [18]. In the context of feedback and goals, these plans may increase goal-directed behaviours by increasing self-efficacy. Action plans can also facilitate success by increasing goal-commitment to overcome barriers such as distraction or fatigue; implementation plans in particular seem to increase goal-directed behaviours [19]. Implementation intentions are developed through if/then statements, wherein the participant must connect a situation (if) with a behavioural response (then). With some effort (*i.e*., considering and writing down the plan), the connection made between contextual cues and an action plan can become automatic, thereby increasing goal attainment without conscious intent.

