### Study objectives and hypotheses

For family physicians receiving performance feedback reporting the percentage of their patients with diabetes and/or IHD who are achieving quality targets, the addition of a theory-informed worksheet designed to facilitate goal setting and the development of action plans will lead to changes in behaviour and improved outcomes. A second hypothesis is that those physicians in the intervention group who properly complete the worksheet will have the largest improvement in outcomes. Finally, we aim to explore qualitatively the perceived barriers to behaviour change in response to feedback reports and the preferences of family physicians with regard to feedback design.

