## Methods

### Study design

This is a mixed methods study built around a pragmatic, cluster-trial with two arms; one group will receive 'simple' feedback, while the other will receive 'enhanced' feedback. Allocation is at the practice level to reduce risk of contamination and the intervention directed at the physician level. In Ontario, family physicians do work in groups, but this generally involves sharing administrative resources, not patients. The usual approach is for chronic conditions to be dealt with by the personal physician, while acute issues may be dealt with by the available physician. Therefore, we believe that an intervention aimed at the physician rather than the entire clinic is appropriate. The analysis will be at the patient level, including both disease-level outcomes of BP and low-density lipoprotein cholesterol (LDL) and a composite score of process variables, as detailed in the 'outcomes' section.

The lack of a control group receiving no feedback at all is both necessary (because participants expected something in return for contributing data) and pragmatic (because most quality improvement interventions include some degree of feedback, making this the 'usual care' comparator) [23]. In particular, the Ministry of Health and Long-Term Care in Ontario (MOHLTC) is providing feedback reports to all family physicians as part of its diabetes strategy [24].

This study has received approval from the Research Ethics Office at Sunnybrook Health Sciences Centre (271-2006) and is registered with ClinicalTrials.gov (NCT00996645).

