Based on our review of the literature, the largest effects from goal setting and action planning seem to come from actually developing the plan (and linking it to a specific context to carry it out). For this reason, we chose not to provide participants with a list of possible actions. The participants, not the investigators, decide how to improve upon a care gap that they identify as important. Important mediators of the success of implementation intentions seem to be participant adherence to instructions to develop an appropriate plan, participant self-efficacy, and the inclusion of 'coping plans' to help participants plan ahead for situations that could interrupt goal-oriented behaviours [32,33]. These factors will be addressed explicitly in this trial by: offering six 'Main-Pro-C' [34] continuing medical education credits to encourage full completion of the worksheet and to permit monitoring of plans by the investigators; allowing participants to set their own goals for improvement; and requiring participants to develop a coping plan in the intervention worksheet. The format in this aspect of the worksheet is similar to previous studies [33], although to our knowledge the application of this type of intervention to family physicians is novel.

The worksheet in this intervention is similar in concept to commitment-to-change procedures that are increasingly used in the continuing medical education field, based on multiple theories related to adult learning [35]. Rigorous evaluations of such procedures are few, but one study indicated that commitment-to-change can mediate the effect of an educational intervention for prescriptions [36]. Although a signature has not been proven to increase the effectiveness of the commitment-to-change procedure [37], it is included in the worksheet because it offers an opportunity to explicitly use the word 'commitment;' this is thought to be a necessary feature for the procedure to successfully generate behaviour change (see Additional File 2 for prototype of worksheet) [38]. We tested the worksheet design and all other intervention materials with a group of non-participating family physicians and they found it easy to use. Specifically, they reported that they found the instructions clear and advised no changes to the design. To our knowledge, the application of this type of worksheet as a means of 'enhancing' the effectiveness of audit and feedback is novel.

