## Analysis

Descriptive statistics will be calculated for all variables of interest. Continuous measures will be summarized using means and standard deviations whereas categorical measures will be summarized using counts and percentages.

We hypothesize that the enhanced feedback intervention will lead to greater improvements in quality of care for patients with diabetes and/or IHD. The analysis to test this hypothesis will be carried out using multilevel hierarchical modeling (using the generalized estimating equation approach) to control for the effects of clustering as well as adjusting for multiple covariates, including the variables used in the minimization (baseline values for BP, LDL, the composite process score, and the number of patients with diabetes and/or IHD). Analysis will be performed on an intention-to-treat basis. No interim analyses are planned. Prior to analysis, other covariates will be assessed for the presence of multicollinearity; when the tolerance statistic value < 0.4 only one member of a correlated set will be retained for the model. Primary analyses will be conducted on patient level variables, combining patients with diabetes and/or IHD. Sub-group analyses will be performed on patients with only IHD, only diabetes, or both, to assess the same outcome variables.

The efficacy of the worksheet intervention will be assessed as a planned secondary analysis in two ways. First, we will test whether full completion of the worksheet resulted in improved outcomes. Full completion of the worksheet will be evaluated according to whether they declared specific and measurable goals, completed all sections of the action plan, and confirmed their commitment with their signature. Second, we will examine if physicians achieved greater improvements in the specific clinical topics that they chose to target using the worksheet.

All analyses will be carried out using the SAS Version 9.2 statistical program (SAS Institute, Cary, NC, USA).

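### The worksheet-completion analysis is worded as a causal test of efficacy, but completion is self-selected after allocation, so it can support only an association

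*Protocol article*

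**What the plan says.** In the protocol article, the Analysis section introduces the worksheet analyses with "The efficacy of the worksheet intervention will be assessed as a planned secondary analysis in two ways". The first of the two is: "First, we will test whether full completion of the worksheet resulted in improved outcomes". A physician counts as a full completer if the goals are specific and measurable and if he or she "completed all sections of the action plan, and confirmed their commitment with their signature".

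The matching hypothesis, under Study objectives and hypotheses, is that "those physicians in the intervention group who properly complete the worksheet will have the largest improvement in outcomes".

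Under Intervention, only the enhanced arm receives the worksheet, and the trial offers "continuing medical education credits to encourage full completion of the worksheet". Study design states what was allocated: "Allocation is at the practice level to reduce risk of contamination and the intervention directed at the physician level".

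For the main hypothesis the Analysis section says "Analysis will be performed on an intention-to-treat basis". The covariates it names are baseline BP, LDL, composite score and number of eligible patients, plus other covariates that are not listed.

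Nothing marks the completion analysis as exploratory or associational, and the limitations in the Discussion do not mention it.

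**The concern.** Completion happens after allocation, in one arm only, and by the physician's own decision. Physicians who fill in every section and sign may be those who would have improved their care anyway. A comparison defined by completion does not have the protection that allocation gives to the comparison between arms.

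The plan nevertheless uses causal language: it calls the analysis an assessment of efficacy and asks what completion resulted in. Followed as written, it could support a statement that the worksheet works when properly completed, although the data would look much the same if engaged physicians simply do better. That statement would be most tempting if the arms did not differ.

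**Working it through.** **1. Which comparison is protected by allocation**

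| Comparison | How the groups are formed | Causal reading supported? |
|---|---|---|
| Enhanced v simple arm | Minimization of practices | Yes |
| Completers v non-completers, enhanced arm | Physician's choice | No |
| Completers v whole simple arm | Choice on one side only | No |

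The protocol's own theory supplies the confounder. It says that recipients unhappy with their results will change behaviour "if they are committed to the goal and if they meet a threshold level of self-efficacy for that task". A signed commitment is part of the definition of full completion. The exposure is thus partly a marker of a trait that the protocol expects to drive the outcome. The named covariates contain no measure of that trait.

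**2. The plan's figures that supply inputs**

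The plan states no figure for this analysis. Its systolic BP sample size (SD 20, difference 7, ICC 0.05, mean cluster size 328) reproduces:
- unclustered total for 80% power, two-sided 5%: 258;
- VIF = 1 + (328 − 1) × 0.05 = 17.35, given as 17.4;
- 258 × 17.4 = 4,489 patients; 4,489 / 328 = 13.7 clusters.

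**3. Illustration of self-selection with no true effect**

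Assumptions that are not in the documents:
- the ICC of 0.05 applies between physicians, so σ = 20 × √0.05 = 4.47 mmHg;
- the enhanced arm has half of the 54 physicians (27), with about 4,593 / 54 = 85 patients each;
- motivation correlates r = 0.5 with the tendency to complete;
- motivation explains a share v of between-physician variance, from 10% to 50%;
- there is no baseline adjustment.

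For completion share p, let φ be the normal density at the point that cuts off p. The spurious gap is then:
- against non-completers: r × φ / [p(1 − p)] × √v × σ;
- against the simple arm: r × φ / p × √v × σ.

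At p = 50%, φ = 0.399:
- non-completers: 0.5 × 0.399 / 0.25 = 0.80. Multiplying by √0.1 × 4.47 = 1.41 gives 1.1 mmHg; by √0.5 × 4.47 = 3.16 gives 2.5 mmHg.
- simple arm: 0.5 × 0.399 / 0.5 = 0.40, giving 0.6 to 1.3 mmHg.

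Over p from 30% to 70% the ranges are 1.1 to 2.6 mmHg against non-completers and 0.4 to 1.8 mmHg against the simple arm. The first range is 16% to 37% of the 7 mmHg target.

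Rejection rate of a nominal 5% physician-level t-test at p = 50% (5,000 simulated trials per cell):

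| v | Completers v non-completers | Completers v simple arm |
|---|---|---|
| 0 | 5.4% | 5.4% |
| 10% | 8.2% | 6.5% |
| 25% | 14.1% | 7.8% |
| 50% | 25.6% | 10.6% |

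**4. What a complier-average estimate would do**

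The simple arm gets no worksheet, so non-compliance is one-sided. The estimate is the ITT effect divided by the completion share c: multipliers 1/0.3 = 3.3, 1/0.5 = 2.0 and 1/0.7 = 1.4. It rescales the ITT result and carries the same test, so its false-positive risk is that of the ITT test.

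**The case against.** The strongest reply is that this is a secondary analysis, that the ITT comparison between arms stands untouched, and that a condensed article may leave comparator and model to the full plan. Looking at outcomes by adherence is a fair process question, since the Intervention section treats adherence as a mediator. The second hypothesis, read literally, predicts only an ordering. Baseline values and characteristics such as years in practice could be adjusted for. The companion analysis, of topics that physicians chose to target, would hold general motivation largely constant if done within physician, although topic choice is itself selected.

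Most of this stands, and the unnamed comparator is not held against the article. But the causal wording is the article's own, and it fails under either comparator. Adjustment for baseline performance leaves unmeasured motivation in place.

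A reader might infer more than the documents support:

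- **That this result would decide whether the worksheet is rolled out.** The Discussion ties next steps to whether the intervention works, which the main analysis tests.
- **That self-selection could mimic the whole target of 0.3 composite points.** With SD 1.61 and ICC 0.0059 to 0.01, the between-practice SD is 1.61 × √0.0059 = 0.12 to 1.61 × √0.01 = 0.16. A gap of 0.3 would be about 1.9 to 2.4 of those SDs. Physician-level variation is not given and may be larger, but nothing supports 0.3 as a likely bias.
- **That a complier-average estimate cannot produce a false positive.** It can, exactly as often as the ITT test.
- **That a complier effect of full completion would settle the matter.** It assumes that a partly completed worksheet does nothing. That is doubtful: a physician who sets goals and plans but does not sign counts as a non-completer, and the Intervention section says that a signature is not proven to add effect.

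**Conclusion.** The point holds as a fault in how a secondary analysis is framed. The planned completion analysis cannot show what completion caused, because completion is voluntary, follows allocation, and is plausibly driven by traits that the protocol itself links to behaviour change.

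The size of the bias cannot be obtained from the documents. The 1.1 to 2.6 mmHg and the 8% to 26% rejection rates against non-completers rest on the assumed correlation, variance shares and physician-level ICC, without baseline adjustment; they show that the problem is not negligible, not how large it is here. The direction probably favours completion, but this is not certain: physicians might, for example, complete the worksheet because their care is hardest to improve.

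The primary analysis and the sample size are not affected.

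**What to change.** In the Analysis section, for this analysis:

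1. Remove the description as efficacy and the wording that completion resulted in improvement.
2. Report the completer comparison as an exploratory association, adjusted for baseline values, and say that physician motivation is unmeasured.
3. State that causal conclusions about the worksheet rest on the allocated comparison.
4. If a causal estimate of worksheet use is wanted, add a supplementary complier-average effect with arm allocation as the instrument. Define compliance as any completion at any of the six-monthly cycles, so that the assumption of no effect in non-compliers is more plausible, and state that assumption.

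Items 1 to 3 cost only wording. Item 4 costs one further model. Its estimate will be imprecise with about 14 clusters, has the same false-positive risk as the ITT test, and does not itself test the second hypothesis about which enhanced-arm physicians improve most. That question remains descriptive.

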There is some empirical evidence that intensive interventions that help participants set practice improvement plans in response to feedback can improve outcomes [20], possibly by increasing goal commitment and self-efficacy. Recognizing that feedback alone is sometimes not enough to change provider behaviours, further improvements have been found by pairing feedback with more intensive (and expensive) co-interventions, such as educational outreach visits [21]. Although these intensive interventions are rarely explicitly informed by theory [22], they presumably work because they help participants to take action to improve outcomes for patients. The assumption is that healthcare providers intend to provide consistently high quality of care, but are uncertain how to change their behaviours to accomplish this feat. Therefore, an intervention aiming to close this intention-behaviour-gap could be very effective. In this study, it is expected that the feedback reports will draw family physicians' attention to a discrepancy between actual and ideal care -- *e.g*., fewer patients than expected are at target blood pressure (BP) -- and that a theoretically-informed worksheet can be developed to facilitate goal-setting and action-plans to enhance the likelihood that they will take action to close this gap (*e.g*., implement systems to monitor at-risk patients with BP above target). See Figure 1 for an illustration of potential role of goal-setting and action plans on effectiveness of feedback.

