### Intervention

The intervention has been developed through an iterative process. The materials for dissemination were designed after a review of the literature and consultation with experts from continuing medical education, health psychology, and knowledge translation.

Participants in both arms of the trial will each receive an information package by courier every six months for two years with multiple components, including a one-page cover letter, a one-page explanation of how the patient information was identified from EMRALD, a one-page handout reviewing generic clinical and quality improvement strategies for patients with diabetes and/or IHD (based in part on the chronic care model [29]), and two separate feedback reports. The first report will describe the percentage of the participating physician's patients with diabetes who are meeting evidence-based quality targets. The second will present similar information regarding their patients with IHD. The quality targets used were chosen to be consistent with those used by concurrent quality improvement interventions in Ontario (Quality Improvement and Innovation Partnership) [30] and with current guidelines (see Outcomes section below). The reports will present information comparing the performance achieved by the participating physician to the average achieved by the top 10% of participants for any given measure. This type of comparator is similar to the achievable benchmark of care previously shown to improve the effectiveness of feedback reports [31]. See Additional File 1 for prototype feedback reports.

Participants randomized to the enhanced feedback arm will receive exactly the same materials as the simple feedback arm, plus a one-page worksheet. This theory-informed worksheet is designed to facilitate participants in setting specific but challenging goals and help participants develop action-plans through the creation of implementation intentions (see Additional File 2 for prototype of worksheet). An evaluation to assess the theoretical validity of the intervention will be reported separately.

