## Discussion

With the use of audit and feedback interventions likely to increase over time, there is a need to understand how their design effects the behaviour of primary care providers. This project will play a role in learning how to generate feedback reports that are useful for family physicians. Even if the trial is negative, the qualitative process evaluation will provide useful information and generate new study questions. Future studies may then compare the cost-effectiveness of using interventions similar to the one described in this trial against more intensive interventions such as academic detailing or practice facilitators.

There are also some important limitations that warrant discussion. One concern regarding generalizability is that it is possible that there will be a specific interaction between the worksheet intervention and the feedback such that adding the worksheet to other designs/types of feedback or other interventions may not work as well. It is also important to note that participants in EMRALD are a convenience sample of Ontario family physicians using Practice Solutions^®^. Therefore, findings from this group will not be strictly generalizable to other providers who use different EMR systems, or to those not using EMR at all. In addition, many of the clinics are involved in other quality improvement interventions. Thus, these clinics may be more innovative and may also be achieving a higher level of evidence-based care than most other primary care providers.

Perceived data accuracy has been identified as an essential feature for acceptance of feedback reports [69], and previous studies have shown that data quality from EMRs are uncertain [70]. While we have validated algorithms for identifying patients who have diabetes and/or IHD in this database, the automated chart audits that are the basis for both the intervention and the outcome assessment may occasionally have errors. However, there is no reason to believe that any such errors occurring in the data abstraction process represent a risk for bias; any problems with the algorithm would be equally likely to occur in either arm of the trial.

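### The secondary analysis of improvement on self-chosen topics is open to regression to the mean, and needs each indicator's own baseline and a simple-arm comparison before it can be read as worksheet efficacy

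*Protocol article*

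**What the plan says.** The Analysis section announces two secondary looks at the worksheet: "The efficacy of the worksheet intervention will be assessed as a planned secondary analysis in two ways". The first concerns full completion of the worksheet. The second is the one at issue: "we will examine if physicians achieved greater improvements in the specific clinical topics that they chose to target using the worksheet". The article names no comparator, change measure or model for it.

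Four other statements show how a topic comes to be chosen and how change on it is then measured:

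- The theory section says of the trial's mechanism that "it is expected that the feedback reports will draw family physicians' attention to a discrepancy between actual and ideal care".
- The Intervention section says that each report presents information "comparing the performance achieved by the participating physician to the average achieved by the top 10% of participants for any given measure".
- On the choice itself, the Intervention section says: "The participants, not the investigators, decide how to improve upon a care gap that they identify as important".
- The Discussion refers to "the automated chart audits that are the basis for both the intervention and the outcome assessment may occasionally have errors", so selection and outcome share one data source.

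Only one arm makes a choice: "Participants randomized to the enhanced feedback arm will receive exactly the same materials as the simple feedback arm, plus a one-page worksheet". The baseline covariates in the Analysis section (BP, LDL, composite process score, number of eligible patients) are given for the between-arm model. None is defined as the baseline of whichever indicator a physician picked.

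**The concern.** A physician's score on one indicator is a proportion over a modest panel, so part of any low score is chance. If low scores attract the choice, chosen topics are enriched for unlucky readings. At the next audit the chance part fades and those topics rise more than the others, with no change in care. The same audit system supplies both readings, so nothing in the measurement separates this drift from real improvement.

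The direction is predictable: it favours the worksheet. The article presents the result as evidence on efficacy, so a positive finding under the null would be reported as support for goal setting. The simple arm, which has no worksheet, has no chosen topics that would reveal the drift unless a comparison is built for the purpose.

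**Working it through.** **Inputs from the protocol article.** Table 1 gives 4,593 patients with diabetes or IHD, 14 clinics and 54 physicians. 4,593/14 = 328 reproduces the mean cluster size in the Sample size section. 4,593/54 = 85 patients per physician. The same section gives an ICC of 0.0059, rounded up to 0.01, for the process score and a presumed 0.05 for BP. The article gives no figure for the analysis at issue, so there is none to reproduce.

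**Assumed inputs.** 60% of patients at target; between-physician SD of 5 to 8 points per indicator; K = 4 or 6 indicators; the lowest observed one chosen; carry-over ρ (share of patients whose status is unchanged between audits) of 0, 0.5 or 0.7; no true change. The SDs correspond to ICCs of 25/2,400 = 0.010 and 64/2,400 = 0.027, inside the protocol's 0.01 to 0.05. Applying practice-level ICCs for other measures to single indicators at physician level is itself an assumption.

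**Step 1: how much of a score is chance.** Reliability = m × ICC / (1 + (m − 1) × ICC) with m = 85 gives 0.34 (ICC 0.0059), 0.46 (0.01) and 0.82 (0.05). On process measures, then, about half to two-thirds of a physician's observed deviation may be noise.

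**Step 2: expected spurious gain.** Sampling SD = √(0.6 × 0.4/85) = 5.3 points. Total SD = √(SD_between² + 5.3²). Noise share = 5.3²/total SD². In total-SD units, the lowest of K independent normal readings lies below the mean of the others by 1.37 (K = 4) or 1.52 (K = 6). Spurious gain = (1 − ρ) × noise share × that distance × total SD.

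| Between SD | Total SD | Noise share | K | ρ = 0 | ρ = 0.5 | ρ = 0.7 |
|---|---|---|---|---|---|---|
| 5 | 7.3 | 0.53 | 4 | 5.3 | 2.7 | 1.6 |
| 5 | 7.3 | 0.53 | 6 | 5.9 | 2.9 | 1.8 |
| 8 | 9.6 | 0.31 | 4 | 4.0 | 2.0 | 1.2 |
| 8 | 9.6 | 0.31 | 6 | 4.5 | 2.2 | 1.3 |

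Example (SD 5, K = 4, ρ = 0): 0.53 × 1.37 × 7.3 = 5.3 points. A binomial simulation of the same set-up agreed (4.1 to 6.0, 2.0 to 3.0 and 1.2 to 1.8 points).

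**Step 3: weaker selection, by the same simulation.**

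| Scenario | ρ = 0 | ρ = 0.5 | ρ = 0.7 |
|---|---|---|---|
| Half of choices follow the lowest score | 2.0–3.0 | 1.0–1.5 | 0.6–0.9 |
| Indicator means spread over 45–75%, lowest raw score chosen | 2.1–3.1 | 1.0–1.6 | 0.6–1.0 |
| Choice unrelated to score | 0 | 0 | 0 |

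**Step 4: adjustment.** Regressing follow-up on the indicator's own baseline, indicator, arm and a chosen flag left at most about 0.3 point of bias, both in the chosen coefficient and in arm plus chosen.

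**The case against.** The strongest reply is that the article states no contrast. A reader might infer that it commits to comparing chosen with unchosen topics within physicians. It does not: the greater improvement could be relative to simple-arm physicians, or to enhanced-arm physicians who did not pick that topic. The model may stand in a fuller plan. This stands, and it is why the analysis is open to the bias and cannot be said to have it built in. What remains is that the article fixes the quantity of interest and labels it efficacy, and that the obvious reading carries a bias of known direction.

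A reader might also infer that physicians always pick their largest gap. No statement says so. They pick a gap they find important, and the theory section suggests other drivers, such as belief that the effort will succeed. This stands as well, and it shrinks the bias as in step 3. It removes the bias only if choice ignores the report, which is contrary to the trial's own rationale.

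Third, full re-drawing of patient status is implausible for rostered patients with chronic disease when several indicators are active prescriptions. That is fair, and the carry-over columns deserve more weight than the ρ = 0 column. In the other direction, diabetes and IHD are reported separately, so the panel behind one indicator can be smaller than 85.

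**Conclusion.** The point holds as a vulnerability of one secondary analysis. If choice follows the observed gap, an unadjusted chosen-versus-other comparison shows a spurious gain of roughly 1 to 3 percentage points with 50 to 70% carry-over, and 4 to 6 points with none. It is less if indicator means differ or choice follows the gap only partly, and nil if choice is unrelated to it. All inputs except the 85 patients per physician are assumed, so these are illustrative ranges.

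Two stronger conclusions are tempting. One is that the artefact matches the 5% median audit-and-feedback effect quoted in the Background. That needs little or no carry-over and near-consistent choice of the worst score, neither of which the article supports. The other is that this is the main evidence on the goal-setting mechanism. It is the second of two secondary analyses, and the stated second hypothesis concerns worksheet completion. The allocated comparison between arms is not affected.

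**What to change.** Specify the analysis at the level of physician and indicator:

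follow-up = indicator effect + β × that indicator's own baseline + γ × arm + δ × chosen, with clustering handled by practice.

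Baseline should be the audit reading shown in the report from which the topic was picked.

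The main estimate should be γ + δ, which compares chosen topics with simple-arm physicians on the same indicator at the same baseline. The chosen coefficient δ alone is still a contrast within the enhanced arm, because only that arm can have chosen topics.

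Label the analysis exploratory. Baseline adjustment deals with selection on the observed score, but not with other reasons for choosing a topic, such as motivation. Report any unadjusted chosen-versus-unchosen contrast as descriptive only.

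The cost is analysis wording and a little extra modelling. No new data are needed, since the simple arm's indicator results are already produced for its reports.
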